## 5.2 Feature description

*Test-Latency:*

Mean MWT- or DS-MWT-latencies are determined by averaging latencies from four max. 40 min test- sessions determined by AASM-criteria (REF,) and previously reported additional/complementary parameters (e.g., sleep accidents with closed eyes, (1)) for the two tests, respectively.

*Driving Parameters*

We will collect multiple driving parameters, such as the standard deviation of lane position, SDLP, the standard deviation of velocity, SDS, number of lane departures, and LD. Collected parameters will also be used as one criterion to determine the sleep-accident-derived latency for the DS-MWT. IDS

*ET Features*

A recent review showed that eye movement features and the sleep-wake predictor model could be used to predict sleepiness (6). For example, the blink rate increases with increased sleep pressure and can be used to assess drowsiness or sleepiness. Other valuable ET metrics (5) for our setting are the saccade latency, saccade peak velocity and smooth pursuit velocity gain, which could also reflect levels of sleep deprivation and extreme sleepiness.

*EEG Features*

EEG recordings are required to determine MWT-latencies, based on precise identification of sleep onset (SO). According to AASM classification, sleep onset is defined as the start of the first epoch scored as any stage other than stage W. In most individuals this will usually be the first epoch of stage N1, characterized by SEM (slow eye movements) and LAMF (low-amplitude, mixed-frequency) in EEG activity. Electrophysiological data collected during both classical MWT and DS-MWT will provide useful additional insights into the sleep-wake transition. For example, microsleep episodes (MSEs), i.e., brief periods of sleep intrusion during wakefulness, may occur even before sleep onset. We will analyze manually- and automatically-detected MSEs (17).

*PSG Features*

PSG monitors multiple physiological signals, including body position, respiratory movement, electrocardiogram (ECG), EEG, electrooculogram (EOG), electromyogram (EMG), breath airflow and oxygen saturation. PSGs provide a reference or baseline for sleep quality of the night prior to each measurement session. Here, the sleep quality will be measured over several criteria such as duration and occurrence of sleep stages; intensity, continuity and stability of sleep episodes etc. Recording of the breath airflow and oxygen saturation will also allow to derive OSA-associated metrics, such as AHI (apnea-hypopnea index), ODI (oxygen desaturation index) etc.

*Biomarkers (saliva, blood)*

Recent studies in proteomics showed promising findings of sleep-deprivation-associated proteins in human blood serum (9-11). For example, 66 out of 494 proteins were found to be differentially expressed proteins (DEPs) after 6 hours of sleep deprivation in (9). Collecting saliva and blood samples (blood, serum or dried spots) in the MWT and DS-MWT setting will be used for targeted screening for sleep-deprivation-associated proteins.

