# Study OBJECTIVES and Design (Zielsetzung der Studie)

## 3.1 Primary Hypothesis and objective

(H_p,1_) Primary hypothesis: no statistically significant difference between MWT- and DS-MWT-latencies (primary outcome measure).

(O_p_) Primary objective: We will determine whether or not – and if yes, to which extent – there is a statistically significant difference between MWT- and DS-MWT-latencies

The primary hypothesis will be tested solely on determined mean latencies and separately from additional, secondary and exploratory analyzes.

(H_s_) Additional, secondary, exploratory hypotheses: There are statistically significant correlations between conditions CPAP-withdrawal vs. CPAP-treatment to secondary test- and performance parameters (see 3.2 secondary outcome measures, see 5.2 Feature Description)

Additional, secondary, exploratory objectives are:

- (O_s-1_) We will explore, whether or not – and if yes, which and to which extent – the **test-sequence** affects MWT- and DS-MWT-latencies and other test- and performance parameters.
- (O_s-2_) We will explore, whether or not – and if yes, which and to which extent – **driving parameters** such as, for example, standard deviation of lateral position, speed, distance and steering wheel angle, SDLP, SDS, SDD and SDSW or integrated driving scores, IDS, correlate to the prior treatment or withdrawal of CPAP and the outcomes of the Epworth Sleepiness Scale (ESS) and Karolinska Sleepiness Scale (KSS) (1). Additionally, time-course-effects of, for example, SDLP will be analyzed using either repeated measures-ANOVA of 10 4-min-long modules comprising the test drive or using paired t-tests of the first and last driven module (1).
- (O_s-3_) We will explore, whether or not – and if yes, which and to which extent – **eye tracking parameters** such as, for example, blink rate, blink duration, eye openness, gaze direction, gaze duration and areas of interests (5, 6), correlate to the prior treatment or withdrawal of CPAP in the driving simulation.
- (O_s-4_) We will explore, whether or not – and if yes, which and to which extent – **EEG-features** that potentially indicate sleepiness, such as, for example, microsleep-like episodes, MSE, or individual signatures of MSE and the sleep/wake transition (7), correlate to the prior treatment or withdrawal of CPAP and the outcomes of the ESS and KSS.

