### 5.1.1 Sample size calculation

The total sample size is N_total_ = 54, consisting of the intervention group N_I_ = 36 and a healthy comparison group N_H_ = 18. (see Figure 2)

Sample sizes N_I_ = 36 for the intervention group were estimated according to formula I considering the randomized crossover RCT study design of a cohort of OSA-patients randomized both to CPAP starting condition and measurement sequence resulting in 4 groups 4 (W-DM, W-MD, C-DM, C-MD, see Figure 2) in two phases and a mixed-model ANOVA analysis. Mixed-model ANOVA accounts for the fact that repeated measures form the same person are correlated, is able to handle any missing values more effectively and considers both fixes and random effects.

[figure not shown]

Formula I

adapted from (13)

- n = Required number of participants per group.
- Z_1−α/2_​ = Z-value corresponding to the chosen significance level (e.g., 1.645 for α = 0.1 two-sided) (14).
- Z_1−β_ = Z-value corresponding to the desired power, 1.28 for 90% power) (14).
- σ = Standard deviation of the measurements = 13.5 minutes (from Bonnet & Arand) (15)
- ρ = Intra-class correlation (ICC) or correlation between repeated measures within the same participant.
- Δ = Equivalence margin or effect size = 1 pooled SD = 13.5 minutes (from Bonnet & Arand) (15)

For the sample size calculations, we use a two-sided α = 0.1 assuming that a potential difference between M and D would have a clear direction and a maximal value (bounded test range) of 40 min for the test latency. When conducting an equivalence test, using a 0.1 two-sided alpha-level effectively matches the 0.05 significance level for each side of the distribution (one for each tail), aligning the rigor of the test with the traditional hypothesis test for no difference. This assumption holds, as the reference standard deviation of 13.5 min was obtained with an equivalently bounded test range. We employ a graphically extracted and pooled standard deviation form Bonnet & Arand (15) (Figure 2 baseline and wake, p 388), the only close-to test-retest data on MWTs available.

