### 5.1.2 Statistical analysis plan

The primary hypothesis will be tested solely on determined mean latencies and separately from additional, secondary and exploratory analyzes. For the primary hypothesis, we will employ a mixed model ANOVA or generalized linear mixed model. All analyzes will be considered significant when p<0.05.

All secondary variables will be analyzed post-hoc for hypothesis-generation rather than formal testing. Collected secondary parameters will be analyzed *post hoc* individually with respect to the experimental condition (D/M) and the participants state (CPAP-treatment or withdrawal). If group-level differences exist we will conduct multiple comparison tests. Time-course-effects of, for example, SDLP are intended to be analyzed using repeated measures-ANOVA between 10 4-min-long modules comprising the test drive or using paired t-tests of the first and last driven module. Integrated Driving Scores (IDS, Z-scores) will be calculated after logistic regression of driving parameters.

For secondary parameter-based models, we will first use linear mixed models and stepwise testing will be based on biological/plausibility justification rather than purely statistical significance.

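### The primary outcome is a mean of latencies capped at 40 min, and nothing planned would tell comparable tests apart from a ceiling effect

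*Protocol*

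**What the plan says.** - Outcome (Protocol 5.2, Test-Latency): the mean latency for each test is "determined by averaging latencies from four max. 40 min test- sessions".
- Data used (5.1.2): "The primary hypothesis will be tested solely on determined mean latencies".
- Model (5.1.2): "For the primary hypothesis, we will employ a mixed model ANOVA or generalized linear mixed model", with "All analyzes will be considered significant when p<0.05".
- Hypothesis (3.1): "Primary hypothesis: no statistically significant difference between MWT- and DS-MWT-latencies (primary outcome measure". The primary objective in the same section also asks how large any difference is.
- Cap (5.1.1): the sample size section recognises "a maximal value (bounded test range) of 40 min for the test latency" and notes that the reference SD of 13.5 min comes from an equally bounded range. It uses the bound to support the planning alpha and SD; 5.1.2 does not take it up. The same section speaks of an equivalence test with a margin of 13.5 min.
- Missing data (5.3): covers participants who leave the trial, not runs that end without sleep onset.

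**The concern.** A run in which the participant stays awake shows that the latency exceeds 40 min, not that it equals 40 min. The protocol does not say how such a run is scored, but a 40-min maximum combined with averaging implies the value 40. Once four runs are averaged, the number that reached the cap is lost. The GLMM option does not recover it, because it is fitted to the same means.

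The direction matters here. The trial hopes to find the two tests comparable. When runs in both tests reach the cap, a shift in underlying time to sleep can only look smaller. Comparable capped means could therefore reflect similar tests, or participants alert enough to reach the ceiling in both. As written, the primary analysis cannot separate the two.

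**Working it through.** **1. The plan's own figure.** Formula I is not legible and no correlation is given, so this step assumes ρ = 0.5. With σ = Δ = 13.5 min, z = 1.645 and 1.28 (5.1.1):

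n = 2(1.645 + 1.282)² σ²(1 − ρ)/Δ² = 2 × 8.56 × 0.5 = 8.56, so 9 per group; 4 × 9 = 36.

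N_I = 36 is reproduced on that assumption. The cap does not make it wrong.

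**2. How much of a shift survives the cap.** For a normal latency with mean μ and SD σ, with a = (40 − μ)/σ:

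E[min(T, 40)] = 40(1 − Φ(a)) + μΦ(a) − σφ(a).

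Take σ = 13.5 and a true difference of 5 min. With uncapped means 42.5 and 37.5, the capped means are 35.77 and 33.27, a difference of 2.50 min. Over a range of assumed centres:

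| Centre of the two uncapped means (min) | Capped difference (min) | Share retained |
|---|---|---|
| 20 | 4.65 | 93% |
| 25 | 4.33 | 87% |
| 30 | 3.85 | 77% |
| 35 | 3.22 | 64% |
| 40 | 2.50 | 50% |

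**3. Effect on the p<0.05 test.** Simulation with 36 patients, two CPAP states and four runs per test per state. Assumed SDs are 8 between patients, 5 between days and 9.65 between runs (√(64 + 25 + 93.1) = 13.5). Withdrawal is assumed to lower latency by 6 min. The uncapped continuation-state MWT mean runs from 22 to 42 min.

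| True difference | Capped difference | Power, capped | Power, uncapped |
|---|---|---|---|
| 0 | about 0 | 4% to 6% (type I error) | about 5% |
| 3 min | 2.7 down to 1.5 min | 68% down to 55% | about 71% |
| 5 min | 4.5 down to 2.3 min | 98% down to 93% | about 99% |

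The cap shrinks the standard error as well as the difference, so power falls far less than the estimate does.

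**4. A difference in the rate of falling asleep.** For exponential latency, E[min(T, 40)] = μ(1 − exp(−40/μ)). Without variation between patients, μ = 60 gives 60 × (1 − 0.513) = 29.2 min and μ = 120 gives 120 × (1 − 0.717) = 34.0 min. Doubling the time to sleep moves the score by 4.8 min.

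With variation between patients (assumed log-SD 0.7 for the patient's rate and 0.3 for the patient-specific ratio, 36 patients, simulator halving the rate):

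| MWT runs reaching 40 min | Difference in capped means |
|---|---|
| 18% | about 6.8 min |
| 50% | about 4.7 min |
| 68% | about 3.0 min |

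Sections 4.3 and 5.1.1 give each patient both tests in both phases, so 2 × 4 = 8 runs per test. Assuming equal rates in both CPAP states, detection at p<0.05 is:

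| MWT runs reaching 40 min | Capped-mean test | Patient-stratified censored rate ratio |
|---|---|---|
| 50% | about 99% | about 99% |
| 68% | about 91% | about 95% |

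These percentages carry simulation error of a point or two.

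**The case against.** The strongest reply is that the protocol compares the scores the two tests yield. For that quantity min(T, 40) is fully observed and the capped mean is unbiased. The planning SD, and so the 13.5-min margin, also sit on a bounded scale. This stands: the capped mean is a proper primary outcome. What remains is that the protocol never declares this target, and that a small difference in scores near the ceiling says little about the difference in time to sleep.

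Stronger readings that a reader might infer, and why the documents do not support them:

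- **The primary test is invalid or badly underpowered.** Type I error stays near 5%. With eight runs per test, a halved sleep rate is usually detected, and the censored model adds only a few points of power.
- **Most runs will reach the cap.** The protocol gives no such share. In the 50% and 68% settings the SD of patients' capped MWT means is about 8.7 and 7.0 min, below the planning SD of 13.5. The comparison is indirect, since 5.1.1 does not say whether 13.5 refers to single runs or to means, but it is a reason not to treat heavy capping as likely.
- **False equivalence occurs at a known rate.** 5.1.2 specifies a test at p<0.05. The only margin is the 13.5 min in 5.1.1, which sits on the bounded scale, so pass rates against a narrower margin would judge a rule the trial does not have. Whether 13.5 min is too wide is a separate question.
- **Simulator runs stopped early will be scored as sleep.** The protocol says neither that nor the opposite, and such handling commonly belongs in an SAP.

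**Conclusion.** The point holds as one of interpretation, not of test validity. The primary analysis rests only on means of latencies capped at 40 min. In a trial that hypothesises equality, the cap pulls a real difference in time to sleep toward that result, without any planned output that would show it.

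The size cannot be fixed from the documents. A uniform 5-min shift keeps 93% of its size if latencies centre near 20 min and 50% if they centre at 40 min. A halved sleep rate appears as about 6.8 down to 3.0 min as the capped share of MWT runs rises from 18% to 68%. These figures rest on assumed normal or exponential latencies, the assumed variance components and, for the detection rates, equal sleep rates in both CPAP states. If few runs reach 40 min, the matter is minor. The trial should be able to show which case applies.

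**What to change.** In 5.1.2 and 5.2:

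1. State that the mean latency capped at 40 min is the target of the primary analysis, and that a run without sleep onset is scored 40.
2. Report the share of runs reaching 40 min for each test and CPAP state.
3. Pre-specify one supportive run-level time-to-sleep analysis. Censor runs without sleep at 40 min; use a participant frailty or stratum; include test, CPAP state, phase, day and run as factors. Report the DS-MWT/MWT rate ratio with its interval.
4. Say in advance that any comparability statement will be qualified if the capped share is high or the rate ratio shows a difference. Agreement on both scales need not be a formal success criterion; no margin exists for the rate ratio.

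The cost is one extra model on data already collected, with no change to visits or sample size; 5.1.2 already plans exploratory run-level work on sleep onset. The downside is a possibly more cautious comparability statement.

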## 5.3 Handling of missing data and drop-outs

Missing datasets due to participants’ withdrawal from the trial will not be multiply imputed due to the low sample size and inherently low statistical power. All available data will be used, if possible, for statistical analysis. Drop-outs during the study phase will be replaced by recruitment of new participants from the accessible participant pool, if possible.

# Regulatory Aspects AND SAFETY

## 6.1 Local regulations / Declaration of Helsinki

This study is conducted in compliance with the protocol, the current version of the Declaration of Helsinki, the ICH-GCP, the HRA as well as other locally relevant legal and regulatory requirements.

## 6.2 (Serious) Adverse Events and notification of safety and protective measures

An Adverse Event (AE) is any untoward medical occurrence in a patient or a clinical investigation subject which does not necessarily have a causal relationship with the trial procedure. An AE can therefore be any unfavorable or unintended finding, symptom, or disease temporally associated with a trial procedure, whether or not related to it.

A Serious Adverse Event (SAE) (ClinO, Art. 63) is any untoward medical occurrence that

- Results in death or is life-threatening,
- Requires in-patient hospitalization or prolongation of existing hospitalization,
- Results in persistent or significant disability or incapacity, or
- Causes a congenital anomaly or birth defect.

Both Investigator and Sponsor-Investigator make a causality assessment of the event to the trial intervention, (see table below based on the terms given in ICH E2A guidelines). Any event assessed as possibly, probably, or definitely related is classified as related to the trial intervention.

| **Relationship** | **Description** |
| --- | --- |
| Definitely | Temporal relationship  Improvement after dechallenge*  Recurrence after rechallenge  (or other proof of drug cause) |
| Probably | Temporal relationship  Improvement after dechallenge  No other cause evident |
| Possibly | Temporal relationship  Other cause possible |
| Unlikely | Any assessable reaction that does not fulfil the above conditions |
| Not related | Causal relationship can be ruled out |
| *Improvement after dechallenge only taken into consideration, if applicable to reaction | |

Both Investigator and Sponsor-Investigator make a severity assessment of the event as mild, moderate or severe. Mild means the complication is tolerable, moderate means it interferes with daily activities and severe means it renders daily activities impossible. Other grades of severity, such as the terminology from the CTCAE, may be used if appropriately referenced.

**Reporting of SAEs** (see ClinO, Art. 63)

All SAEs are documented and reported immediately (within a maximum of 24 hours) to the Sponsor-Investigator of the study.

If it cannot be excluded that the SAE occurring in Switzerland is attributable to the intervention under investigation, the Investigator reports it to the Ethics Committee via BASEC within 15 days.

Exemptions from expedited reporting may be possible if the SAE is either a clear result of the underlying disease or well-known. Please define those SAEs that are exempted from expedited reporting. A template of the SAE is available at [www.swissethics.ch](http://www.swissethics.ch).

**Follow-up of (Serious) Adverse Events**

Participants who terminate the clinical trial (regularly or prematurely) due to

- reported, ongoing SAE, or
- persistent SAE, e.g. laboratory values or alarming vital signs,

are examined during a follow-up visit. This visit will take place up to 30 days after the end of the study treatment phase. Information from this follow-up visit will be recorded accordingly in the CRF.

[**Notification of safety and protective measures**](https://www.admin.ch/opc/en/classified-compilation/20121176/index.html#a37) (see ClinO, Art 62, b)

If immediate safety and protective measures have to be taken during the conduct of the study, the investigator notifies the Ethics Committee of these measures, and of the circumstances necessitating them, within 7 days.

## 6.3 (Periodic) safety reporting

An annual safety report (ASR) is submitted once a year to the local Ethics Committee by the Investigator (ClinO, Art. 43 Abs 1).

## 6.4 Radiation

n.a., since no interventions with radiation of any kind are planned for this study.

## 6.5 Pregnancy (if applicable)

n.a. since there is no known risk arising from the intervention or study procedure with respect to pregnancy, pregnancy is not an exclusion criterion and will not be handled differently in the analysis.

## 6.6 Amendments

Substantial changes to the study setup and study organization, the protocol and relevant study documents are submitted to the Ethics Committee for approval before implementation. Under emergency circumstances, deviations from the protocol to protect the rights, safety and well-being of human subjects may proceed without prior approval of the Ethics Committee. Such deviations shall be documented and reported to the Ethics Committee as soon as possible.

Substantial amendments are changes that affect the safety, health, rights and obligations of participants, changes in the protocol that affect study objective(s) or central research topic, changes of study site(s) or of study leader and sponsor (ClinO, Art. 29).

A list of substantial changes is also available on [www.swissethics.ch](http://www.swissethics.ch).

A list of all non-substantial amendments will be submitted once a year to the competent EC together with the ASR.

## 6.7 Notification and reporting upon completion, discontinuation or interruption of the study

Upon regular study completion, the Ethics Committee is notified via BASEC within 90 days (ClinO, Art. 38).

The Sponsor-Investigator may terminate the study prematurely according to certain circumstances, e.g.

- Ethical concerns,
- Insufficient participant recruitment,
- When the safety of the participants is doubtful or at risk (e.g. when the benefit-risk assessment is no longer positive),
- Alterations in accepted clinical practice that make the continuation of the study unwise, or
- Early evidence of harm or benefit of the experimental intervention

Upon premature study termination or study interruption, the Ethics Committee is notified via BASEC within 15 days (ClinO, Art. 38).

A final report is submitted to the Ethics Committee via BASEC within a year after completion or discontinuation of the study unless a longer period is specified in the protocol (ClinO, Art. 38).

## 6.8 Insurance

The insurance is covered by the "Insurance for Clinical Trials and Non-Clinical Trials" of the Zurich Insurance Company. This covers all damages associated with the clinical trial. In the event of study-related damage or injuries, the liability of this institution provides compensation, except for claims that arise from misconduct or gross negligence.

Participants must strictly follow the instructions of the study team in order not to jeopardize insurance coverage. Furthermore, they may not undergo any other medical treatment during the clinical trial without the consent of the investigator (except in emergencies). They must inform the investigator immediately of any emergency treatment. In the event of health problems or other damage during or after participation in the study, the subject must be informed. In the event of claim, representatives of the insurance company are also given access to the medical data via the examiner, but only to the extent necessary to settle the claim. A copy of the insurance certificate is stored in the test center folder.

